## Abstract

**Background:**

Smoking cessation is the most common preventative for an array of diseases, including lung cancer and chronic obstructive pulmonary disease. Although there are many efforts advocating for smoking cessation, smoking is still highly prevalent. For instance, in the USA in 2015, 50% of all smokers attempted to quit smoking, and only 5–7% of them succeeded – with slight deviation depending on external assistance. Previous studies show that computer-tailored messages which support smoking abstinence are effective. The combination of health recommender systems and behavioral-change theories is becoming increasingly popular in computer-tailoring. The objective of this study is to evaluate patients’s smoking cessation rates by means of two randomized controlled trials using computer-tailored motivational messages. A group of 100 patients will be recruited in medical centers in Taiwan (50 patients in the intervention group, and 50 patients in the control group), and a group of 1000 patients will be recruited on-line (500 patients in the intervention group, and 500 patients in the control group). The collected data will be made available to the public in an open-source data portal.

**Methods:**

Our study will gather data from two sources. The first source is a clinical pilot in which a group of patients from two Taiwanese medical centers will be randomly assigned to either an intervention or a control group. The intervention group will be provided with a mobile app that sends motivational messages selected by a recommender system that takes the user profile (including gender, age, motivations, and social context) and similar users’ opinions. For 6 months, the patients’ smoking activity will be followed up, and confirmed as “smoke-free” by using a test that measures expired carbon monoxide and urinary cotinine levels. The second source will be a public pilot in which Internet users wanting to quit smoking will be able to download the same mobile app as used in the clinical pilot. They will be randomly assigned to a control group that receives basic motivational messages or to an intervention group, that receives personalized messages by the recommender system. For 6 months, patients in the public pilot will be assessed periodically with self-reported questionnaires.

**Discussion:**

This study will be the first to use the I-Change behavioral-change model in combination with a health recommender system and will, therefore, provide relevant insights into computer-tailoring for smoking cessation. If our hypothesis is validated, clinical practice for smoking cessation would benefit from the use of our mobile solution.

**Trial registration:**

ClinicalTrials.gov, ID: NCT03108651. Registered on 11 April 2017.

**Electronic supplementary material:**

The online version of this article (10.1186/s13063-018-3000-1) contains supplementary material, which is available to authorized users.

## Background

Smoking is one of the leading causes of preventable deaths worldwide [1, 2]. Smoking tobacco is proven to have detrimental effects on different organs and is the root cause of several chronic diseases [3]. Among many conditions, smoking can cause cancer, heart disease, lung disease, chronic obstructive pulmonary disease, and it increases the risk of tuberculosis and other diseases related to the immune system [4, 5]. Additionally, secondhand smoking has also been linked to lung cancer, coronary heart disease, respiratory infections, middle ear disease, and sudden infant death syndrome [6].

Despite efforts to increase awareness about the harmful consequences of smoking, smoking cessation rates remain low [7–11]. Various methods have been used to promote smoking cessation in patients, including behavioral therapy, nicotine replacement therapy, and an array of medications. However, the highly addictive chemical nicotine found in tobacco usually causes intense withdrawal symptoms that make it difficult for smokers to quit [12, 13]. These symptoms include headaches, coughing, fatigue, anxiety, depression, and irritability [14]. Withdrawal symptoms act as triggers that increase the urge to smoke, which otherwise are used to relieve negative emotions such as stress [15]. Consequently, there is a high probability of relapse following smoking cessation [16, 17].

### Past studies

Among new smoking cessation methods, computer-tailored interventions have proven to be effective [18–20]. These interventions have been tested both in isolation [18, 21, 22] and in combination with existing methods [23, 24]. The relatively low cost and universal use of mobile phones make them useful to deliver these computer-tailored interventions to patients [25, 26].

With this information, the SmokeFreeBrain (SFB) project [27] assessed the success rate of different interventions for smoking cessation with respect to health economics. The SFB project studied the cost-effectiveness of these interventions and proposed a plan to implement them.

One part of theSFB project was to develop the Mobile Motivational Messages for Change intervention (from now on, 3M4Chan).

The 3M4Chan intervention measures the effectiveness of motivational messages delivered via smartphone to users who wanted to quit smoking. Utilizing the Social, Local, and Mobile (SoLoMo) study’s health-recommender system [28] as a basis, the 3M4Chan intervention uses a modified mobile application (app) to improve its usability, and an includes an inventory of messages based on the successful I-Change model of behavioral change [29–31] which better tailors the motivational messages to remain smoke free. The 3M4Chan intervention also differs from the SoLoMo study in the following aspects: duration of the intervention (6 months in 3M4Chan compared to the 12 months in SoLoMo), follow-up frequency, type of performed assessments and outcome variables, and inclusion and exclusion criteria.

### Hypothesis

We hypothesize that the patients receiving the motivational messages selected by our health recommender system (and grounded in the I-Change model) will have better smoking cessation rates than those who do not receive any messages and also better rates than those who receive motivational messages that are not based on the I-Change model.

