### Planned interventions: control and intervention groups

In the clinical pilot, participants will be randomly allocated into two groups: Participants in the control group will receive the usual care provided at the medical center, while participants in the intervention group will be provided with a mobile app that allows them to receive tailored motivational messages in addition to the usual care. Similarly, participants in the public pilot (those who download the app but do not visit the medical center) will also be randomly allocated into two groups. Those in the control group will receive basic tailored messages without prioritization (the system sends a random message from a list of messages whose contents fit the user profile). Users in the intervention group will receive messages that are more specifically tailored to them (the message to be sent will be determined by its usefulness as reported by others with a similar user profile).

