### Procedure for generating texts

The motivational messages include a wide range of topics, such as physical activity recommendations, diet tips, reminders about the benefits of being a non-smoker, advice for coping with temptation, little known facts about smoking, suggestions to avoid relapses, how to develop skills required to quit effectively, smoking-related social influences, planning actions to change, quitting smoking self-efficacy expectations, and attitudes towards smoking cessation. The recommender system uses de Vries’s I-Change (or Integrated) model [29–31] to tailor messages to users and guide them toward an effective behavioral change.

The messages are designed to cover the different behavioral-change factors – determinants that the I-Change model suggests we should address in order to foster a behavior change. This process consists of two steps. The first one is checking the users’ profile, which was previously answered by the own user through a series of in-app questionnaires. These questions depict the I-Change users’ profile, providing information about their behavioral determinants (attitudes, social support, skills, self-efficacy, intentions, action planning, etc.). After that information is known, the system iterates over a set of 228 different messages that can be sent to the user. Each message is categorized in one of the 131 to different profiles types created based on the I-Change model. For instance, a message could be targeted to young female users with low social support to quit smoking, while other could be targeted to elder male users which have low self-efficacy levels to quit. Then, the system discards those messages which are incompatible with the user we are going to send the message to – for instance, messages targeted to pregnant women if the user is a male –. Finally, the system selects the message which has the highest usefulness rating by other users. The usefulness rating is recorded every time a user receives a message in their phone with a five-star scale.

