At the fourth consultation, physicians will collect information about smoking-related symptoms, treatment adherence, and possible adverse events. Techniques for avoiding the risk of relapse are reinforced. Data about blood pressure, weight, height, and quality of life (using EQ-5D-5 L, IPAQ, and SF-36 questionnaires as well as a questionnaire assessing the satisfaction about the motivational messages received through the 3M4Chan app) will also be collected. All input clinical data will be checked for correctness by two healthcare professionals to ensure quality.

The public pilot will use the same mobile app as the clinical pilot. No additional materials will be used.

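### The hypothesis promises a comparison with messages not based on the I-Change model, but no arm is described as receiving such messages; as described, the public pilot tests how messages are selected

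*Protocol article*

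**What the plan says.** All places are in the protocol article.

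- **Hypothesis.** Two comparators are named: people who get no messages, and a second group over whom the intervention should achieve "better rates than those who receive motivational messages that are not based on the I-Change model".
- **Planned interventions.** Clinical controls get usual care only. Public controls get "basic tailored messages without prioritization", explained as follows: "the system sends a random message from a list of messages whose contents fit the user profile". Public intervention users get the message rated most useful by people with a similar profile.
- **Past studies.** The 3M4Chan intervention is said to include an "inventory of messages based on the successful I-Change model of behavioral change".
- **Procedure for generating texts.** The user profile comes from in-app questionnaires on I-Change determinants. There is one set of 228 messages. "Each message is categorized in one of the 131 to different profiles types created based on the I-Change model". Incompatible messages are discarded, and the highest-rated remaining one is sent.
- **Materials, last paragraph.** "The public pilot will use the same mobile app as the clinical pilot. No additional materials will be used".
- **Abstract, Methods.** Public participants are randomised to a "control group that receives basic motivational messages or to an intervention group, that receives personalized messages by the recommender system". For the clinical intervention arm, the recommender is said to be one that "takes the user profile (including gender, age, motivations, and social context").
- **Design and setting.** The primary objective concerns tailored messages chosen by a recommender system. It does not mention I-Change.

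**The concern.** A hypothesis that names a comparator needs an arm that supplies it. Here the second comparator is defined by the theoretical basis of the messages, while the public control arm is defined by how a message is picked. These are different properties, and the article describes no message set that lacks the I-Change basis.

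What is at stake is attribution. The Abstract's Discussion says practice would benefit if the hypothesis is validated, and the section on expected outputs plans that validation. Read against the hypothesis as written, a positive public-pilot result could be reported as superiority of I-Change messages over other messages, and a null result as their failure. Neither follows if both arms draw on I-Change-based content. A positive result would then support the selection method, and a null result would say nothing about I-Change content.

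**Working it through.** The plan gives no figure on this point, so the check sets the stated comparators against the described arms.

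**Step 1. Arms against comparators** (arm sizes and treatments from Table 1 and the planned-interventions section):

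| Arm | n | Messages | Supplies the no-messages comparator? | Described as supplying the non-I-Change comparator? |
|---|---|---|---|---|
| Clinical control | 50 | none (usual care) | yes | no |
| Clinical intervention | 50 | advanced tailored | no | no |
| Public control | 500 | basic tailored, random draw | no | no (steps 2 and 3) |
| Public intervention | 500 | advanced tailored, ranked by usefulness | no | no |

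The first comparator is met by 1 of 4 arms and the second by 0 of 4.

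**Step 2. Could public control be the second comparator?** It is the only control arm that receives messages. Three statements bear on its content:

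- Its list must fit the user profile, and the only profile described is built from I-Change determinants.
- It uses the same app as the clinical pilot, with no additional materials.
- The one inventory described is I-Change based, and every message in it is assigned to an I-Change profile type.

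The planned-interventions section says what this arm lacks: prioritisation. It does not say that the arm lacks an I-Change basis.

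**Step 3. What differs between the public arms?** The article does not say which profile items filter the control list. Two readings are open:

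- **(a) Same profile in both arms.** The control sequence is then the one in the text-generation section, with the final ranking replaced by a random draw. The arms differ in ranking only.
- **(b) *Basic* means demographics only.** Materials separates basic demographic information from an extended profile. The arms then differ in I-Change profile filtering and in ranking together, and the two effects cannot be separated.

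**Step 4. Does either reading give the promised comparison?** Under both, the only content described is I-Change based, so there is no contrast between I-Change and non-I-Change content. Under (b), controls would receive messages not tailored on I-Change determinants. That would meet the clause only if its words about the model's basis refer to tailoring rather than content, and the effect would still be mixed with that of ranking.

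**The case against.** The strongest reply is that the article never says outright that public controls draw on the 228 messages. The inventory is attached to the 3M4Chan intervention, and the selection procedure described ends in the highest-rated message, which is the intervention arm's rule. One app can hold two lists. The Abstract sets basic messages against personalised ones, and its description of the profile concerns the recommender, not the control list. All of this stands. It means the point can be made only about the trial as described, and that reading (a) cannot be treated as settled.

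A second reply is that I-Change also serves as a tailoring device, so the clause may loosely mean messages not tailored on I-Change. This stands in part: under reading (b) the mismatch shrinks towards imprecise wording. But the clause attaches the model to the messages themselves, and the article does not establish reading (b).

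A third reply is that harm is limited. The primary objective fits the arms. The passages on validation speak of the mobile solution and of recommender-aided messages, not of I-Change content. The randomised comparisons remain interpretable as comparisons of what was assigned. This is correct.

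It cannot be dismissed as detail left to a fuller document. Both the hypothesis and the arms are stated here, and they do not match.

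**Conclusion.** The second half of the hypothesis has no matching arm: 0 of 4 described arms receive messages said not to be I-Change based. As described, the public pilot tests selection by usefulness against random selection, possibly combined with fuller against basic filtering. It does not test I-Change against non-I-Change content.

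This rests on two assumptions. The first is that the single inventory described serves both public arms, which the text supports but does not state. The second is that the hypothesis refers to message content.

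A reader might infer more, and the article does not support it:

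- That ranking is certainly the only difference between the public arms. The control filter is not specified.
- That the public pilot is invalid, or that its 1,000 participants are wasted. The objective and the arms agree, and no bias or loss of power follows. Arm sizes show where the comparison sits, not the amount of harm.

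The consequence is a limit on what the public pilot may conclude, and it deserves correction before results are interpreted.

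**What to change.** 1. In the planned-interventions section, first state which message list the public control uses and which profile items filter it. The wording of the hypothesis depends on this.
2. Then, by a dated amendment, restate the public hypothesis as the actual contrast: recommender-selected versus randomly selected messages, with any difference in filtering named. Drop the comparison with messages not based on I-Change, and limit the public-pilot conclusion to the selection method. The clinical hypothesis (app plus usual care versus usual care) can stay.
3. Because the data-management section mentions monthly interim analyses, state in the amendment whether outcome data by arm had been seen.
4. If controls in fact receive a separate non-I-Change list, keep the hypothesis and correct the descriptions of the control arm and of the message set.

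The cost is wording, one amendment and a registry update, and the Design and setting section already provides for amendments and registry updates. No patients, visits or data are added. The downside is that, unless item 4 applies, the public pilot cannot be used to claim that I-Change content is superior to other content.

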### Need for a trial

Although previous studies have used computer-tailoring [18–20], the I-Change model [23, 32], mobile phones [25, 26], and the health recommender systems to support smoking cessation [33, 34], this is the first study that will bring together all four features. Our study will use a specially designed app called Quit and Return (有戒有還 in Mandarin; hereafter referred to as “the app”) in two methodologically different pilots – a clinical pilot and a public pilot. They will be assessed differently although they will share some common metrics.

If successful, this app could be integrated into treatments for smoking cessation, thereby promoting higher success rates in those attempting to quit. This would result in a better patient health, higher quality of life, lower incidence of smoking-related diseases, and reduced costs in the healthcare sytem.

## Methods

### Design and setting

The primary objective of this study is to assess whether tailored motivational messages supporting smoking cessation—as selected by a health recommender system and delivered by mobile phones to patients—contribute to higher smoking cessation rates.

Secondary objectives include: (1) comparing smoking cessation rates to other user metrics and technical aspects of the system; (2) investigating the relationship between usage of the app used in the 3M4Chan intervention [35] and users’ opinions of messages; and (3) determining if a relation exists between the users’ physical activity levels and their mobile app usage, and their smoking cessation rates.

Both the primary objective and the secondary objectives are common for the clinical and public pilots, although their methodologies and assessments do not completely coincide.

The present document shows the protocol version 1.0.4, 30 May 2018. Major protocol amendments, if any, will be handled by the Taipei Medical University informing any involved stakeholder, and updating the ClinicalTrials.gov registry diligently. Table 1 describes the clincal and public pilot. We followed the Standard Protocol Items: Recommendations for Intervention trials (SPIRIT) guidelines while writing this protocol manuscript (see Additional file 1).

**Table 1 Tab1:** Description of the clinical and public pilot

Name of the pilot	Number of patients	Groups	Treatment	Data to be assessed
Clinical pilot (RCT; 100 patients)	50	Control	Usual care (behavioral therapy and pharmacological treatment)	Smoking cessation rate (clinically validated)
	50	Intervention	Usual care + 3M4Chan app (advanced tailored messages)	Smoking cessation rate (clinically validated)
				Recommender system
				User engagement
				Physical activity
Public pilot (RCT; 1000 patients)	500	Control	m-health (basic tailored messages)	Smoking cessation rate (self-reported)
				Recommender system
				User engagement
				Physical activity
	500	Intervention	m-health (advanced tailored messages)	Smoking cessation rate (self-reported)
				Recommender system
				User engagement
				Physical activity

*RCT* randomized controlled trial

### Target population

The target population is any smoker in Taiwan who want to quit smoking.

### Recruitment procedure

The participants in this study can be divided into two groups: those who participate in the clinical pilot and those who take part in the public pilot. Participants in the clinical pilot will be recruited from smoking cessation units at Taipei Wellcome Clinic and the Taipei Medical University Hospital in Taiwan between 1 September 2017 and 31 July 2018. They will be asked by a nurse or researcher, whether they want to be part of the study in the waiting room before their first visit to the smoking cessation unit. They will be handed written information about the reasoning of the study, and further, they have to sign an informed consent to participate (Additional file 2). The public pilot will be open to any smoker who is willing to quit. In both pilots, each participant must own an Android mobile phone, and accept the terms and conditions of the services provided by the 3M4Chan app. The participants for the public pilot will be recruited online among all the Taiwanese population between 1 September 2017 and 31 July 2018. They will be invited to join the study by downloading the app. These invitations will be done with targeted ads on Facebook and Google, as well as with retargeting banners, which have previously been proven to be successful [36]. In addition, posters and informative leaflets will be distributed at the above-mentioned smoking cessation units and at Health Promotion Administration centers in Taiwan to attract candidates in non-digital environments. A total of four posters, 200 leaflets, and 400 business card-sized advertisements will be printed to disseminate information about the app.

### Inclusion/exclusion criteria

In order to be eligible for the clinical pilot study, each patient has to meet the following inclusion criteria. Participants will be required to be a current smoker aged 20 years or older who owns an Android mobile phone and is able to read Mandarin. Additionally, only those who have smoked at least once per month for the past 2 years and are willing to share information from their medical Electronic Health Record (EHR) with project researchers will be considered. Furthermore, patients will be required to sign an informed consent and agree to be followed up for 6 months.

For the public pilot study, all interested people who download the 3M4Chan app in their Android smartphone, who are aged 20 years or older, and who can read English or Mandarin will be able to join.

